### Non-inferiority margin

The NI margin for mPAP was set at 4 mmHg. This margin reflects a clinically relevant rebound increase while remaining below established treatment thresholds. In our target population, the mean mPAP was approximately 23.6 mmHg. An NI margin of 4 mmHg ensures that the upper limit of the 95% CI remains below 30 mmHg, the threshold for initiating PH therapy (online supplemental figure).^1^

To place this margin in the context of expected interindividual variability, the distribution of mPAP at follow-up was estimated using a pooled SD derived from longitudinal haemodynamic data. Based on this variability, 97.5% of patients are expected to have an mPAP below 38 mmHg at follow-up (23.6+4 + 2×4.9), a threshold that has been associated with worse long-term outcomes in CTEPH.^19^ This approach aims to preserve haemodynamic safety at both the group and individual patient level (online supplemental figure).

The SD of mPAP was estimated from preliminary cohort data in patients meeting the inclusion criterion of mPAP <30 mmHg at 6 months post-BPA (SD 3.43 mmHg). To account for longitudinal variability beyond 6 months, unpublished follow-up data from BPA-treated and PEA-treated patients followed from 6 to 18 months post-intervention, were incorporated (n=40), yielding an SD of mPAP change of 3.8 mmHg, with a correlation of −0.08. The pooled SD was calculated as: $\sqrt{\sigma^{2}combi}=\;\sqrt{3.43^{2}+\;3.8^{2}+\;\left(2\times -0.08\times \;3.43\times \;3.8\right)}=4.9$, which was used for both the sample size calculation and estimation of interindividual variability.

### Sample size calculation

The sample size calculation was performed for the primary endpoint, mPAP at 16 weeks, and for the two secondary endpoints highest in the hierarchy (NT-proBNP and 6MWD). Sample size calculations were performed using the formula: n=f(α,β)×2×σ²/d², where f(α,β) = (Φ⁻¹(α) + Φ⁻¹(β))². For the primary endpoint (mPAP at 16 weeks), assuming a one-sided α of 0.025, power of 90%, SD of 4.9 mmHg and an NI margin of 4 mmHg, 64 participants (32 per group) are required. Allowing for a 10% dropout rate, the target sample size for the primary endpoint is 70 participants.

For NT-proBNP, a NI margin of 30% was chosen, reflecting a clinically meaningful change commonly used in PH and heart failure trials.^20–24^ NT-proBNP values from preliminary data were log-transformed (mean 5.04, SD 1.15), corresponding to a NI margin of 1.51 on the log scale. This yielded a required sample size of 26 participants (13 per group) with 90% power and one-sided α=0.025; accounting for dropout, 29 participants are required. For 6MWD, a NI margin of 15% was used, consistent with widely used definitions of clinical worsening in PAH and CTEPH trials. Using a mean of 467 m and an SD of 95 m of riociguat-treated post-BPA patients derived from a study by Wiedenroth *et al*,^25^ 66 participants (33 per group) are required with 85% power and one-sided α=0.025. After allowing for 10% dropout, 74 participants are required. As the largest sample size was required for 6MWD, the total sample size was set at 74 participants.

NT-proBNP was prioritised in the hierarchical testing strategy because it is an objective biomarker that reflects haemodynamic status. Also, the planned sample size provides greater statistical power for NT-proBNP than for 6MWD.

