**Figure 2 F2:**
[figure not shown]
Outline of study protocol. At the end of study follow-up, participants will also complete a survey assessing satisfaction with the discontinuation strategy. 6MWD, 6-min walking distance; CPET, cardiopulmonary exercise testing; FC, functional class; QoL, quality of life; RHC, right heart catheterisation; TTE, transthoracic echocardiogram.

A predefined safety evaluation is performed at week 8 (±3 weeks). Clinical worsening is defined as the simultaneous occurrence of all three of the following criteria: (1) >15% decrease in 6MWD, (2) progression to WHO functional class III/IV, and (3) increase in NT-proBNP of ≥30% to a level of ≥300 pg/mL. This definition is adapted from prior pulmonary arterial hypertension (PAH) and CTEPH trials and aligns with criteria used in the STELLAR trial.^3
15–18^ If clinical worsening is confirmed, TTE is performed and riociguat is reinitiated in the discontinuation group. Unscheduled evaluations may be performed at the investigator’s discretion in case of suspected clinical deterioration.

At study completion, participants complete a survey assessing satisfaction with the discontinuation strategy. Riociguat may be reintroduced after the end-of-study RHC at the discretion of the treating physician and patient.

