### Objectives and endpoints

The primary endpoint is the between-group difference in mPAP at rest, measured by RHC at 16 weeks. Secondary endpoints for the primary study objective are outlined in table 1.

**Table 1 T1:** Secondary outcomes for the primary study objective

Objectives	Secondary endpoints
To investigate if discontinuation of riociguat is non-inferior to its continuation in CTEPH patients with mPAP <30 mmHg post-BPA	Efficacy endpoints: Between-group differences at 16 weeks for the following parameters in hierarchical order: NT-proBNP (assessed for non-inferiority) 6MWD (assessed for non-inferiority) PVR Cardiac index Between-group differences at 16 weeks in exercise capacity in post hoc analysis: CPET variables: oxygen uptake, workload, heart rate, respiratory exchange ratio, ventilation, oxygen saturation, oxygen pulse, equivalent carbon dioxide Change in modified Borg dyspnoea scale Safety endpoints: Between-group differences at 16 weeks in the following parameters: Number of adverse events and severe adverse events Proportion of participants with mPAP ≥38 mmHg at RHC Proportion of participants meeting the clinical worsening criteria at week 8 Feasibility of the strategy: Is TTE sufficient to replace RHC at the end of study follow-up? The correlation between TTE and RHC parameters Right ventricular systolic pressure Tricuspid annular plane systolic excursion Proportion of participants missed by TTE with mPAP ≥38 mmHg at 16 weeks RHC Is the discontinuation strategy feasible for implementation in clinical practice? Proportion of participants missed by the clinical worsening criteria with mPAP ≥38 mmHg at 16 weeks Participants' satisfaction with the protocol

BPA, balloon angioplasty; CPET, cardiopulmonary exercise testing; CTEPH, chronic thrombo-embolic pulmonary hypertension; mPAP, mean pulmonary artery pressure; 6MWD, 6-min walking distance; NT-proBNP, N-terminal pro-B-type natriuretic peptide; PVR, pulmonary vascular resistance; RHC, right heart catheterisation; TTE, transthoracic echocardiography; WHO, world health organisation.

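### The 30% NT-proBNP margin was converted to 1.51 on the log scale, a ratio of about 4.5 instead of 1.30, so the 26/29 requirement and the power claim for this endpoint are wrong

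*Protocol article*

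**What the plan says.** The section Sample size calculation sets the margin in relative terms: "For NT-proBNP, a NI margin of 30% was chosen, reflecting a clinically meaningful change commonly used in PH and heart failure trials". It moves to the log scale in the next sentence: "NT-proBNP values from preliminary data were log-transformed (mean 5.04, SD 1.15), corresponding to a NI margin of 1.51 on the log scale". From this it derives the requirement: "This yielded a required sample size of 26 participants (13 per group) with 90% power and one-sided α=0.025", and "accounting for dropout, 29 participants are required".

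The same section finds that 6MWD needs the largest sample and takes the trial size from it: "After allowing for 10% dropout, 74 participants are required". It gives two reasons for testing NT-proBNP before 6MWD. One is that NT-proBNP is an objective biomarker of haemodynamic status. The other is that "the planned sample size provides greater statistical power for NT-proBNP than for 6MWD".

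Table 1 (Objectives and endpoints) puts NT-proBNP first and 6MWD second in the hierarchy of secondary endpoints, both tested for non-inferiority. Under Statistical analysis, non-inferiority requires the upper limit of the two-sided 95% CI for the baseline-adjusted difference to stay within the margin.

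Elsewhere the protocol uses 30% on the measured scale. One of the three clinical worsening criteria in Follow-up and safety monitoring is an "increase in NT-proBNP of ≥30% to a level of ≥300 pg/mL".

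**The concern.** A between-group difference in mean log NT-proBNP is the log of a ratio of geometric means. A 30% rise is therefore log(1.30), whatever the mean log is. Taking 30% of the mean log answers a different question, and the result depends on the unit. Reporting in a unit ten times smaller would add ln(10) = 2.303 to the mean log and 0.30 × 2.303 = 0.69 to the margin. A true percentage margin does not move with the unit.

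Two things are at stake. A test against 1.51 could be reported as non-inferiority within 30% when the data allow a far larger rise, in a trial of the safety of stopping treatment. If instead the test is run against a real 30% margin, the first test after the primary has much less power than the protocol says, and in a fixed sequence it stands in front of 6MWD, the endpoint that set the trial size.

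**Working it through.** **Inputs.** From Sample size calculation: log mean 5.04, SD 1.15, log margin 1.51, one-sided α 0.025, power 90%; for 6MWD, mean 467 m, SD 95 m, margin 15%, 33 per group at 85% power. The 10% dropout rate is stated for mPAP and 6MWD. With 74 randomised 1:1 there are 37 per arm, or about 33 after dropout. The true difference is taken as zero, as in the protocol's formula. Two inputs are assumed: natural logs (the base is not stated) and the baseline correlation ρ (not given).

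**1. Source of 1.51.** 0.30 × 5.04 = 1.512.

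**2. The protocol's own figure.** n per group = (1.960 + 1.282)² × 2 × SD² / d² = 10.507 × 2 × 1.15² / 1.51² = 12.19, rounded up to 13, so 26 in total; 26 / 0.90 = 28.9, so 29. Both printed figures reproduce. The formula was applied correctly, and 1.51 is the value that was used, not a misprint.

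**3. What 1.51 means.** exp(1.51) = 4.53, a rise of 353%. The intended 30% is ln(1.30) = 0.262.

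**4. Sample size at a true 30% margin.** 10.507 × 2 × 1.15² / 0.2624² = 403.7, so 404 per group (808 in total, 898 after 10% dropout).

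**5. Power at the planned size.** Power = Φ(d / (SD × √(2/n)) − 1.96). Unadjusted with n = 33: SE = 1.15 × √(2/33) = 0.283, and Φ(0.2624/0.283 − 1.96) = Φ(−1.03) = 15%. With baseline adjustment the residual SD is 1.15 × √(1 − ρ²):

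| Assumed ρ | Residual SD | Power, 33 per arm | Power, 37 per arm |
|---|---|---|---|
| 0 | 1.15 | 15% | 16% |
| 0.7 | 0.82 | 25% | 28% |
| 0.8 | 0.69 | 34% | 37% |
| 0.9 | 0.50 | 57% | 61% |
| 0.95 | 0.36 | 84% | 88% |

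Reading 30% as −ln(0.70) = 0.357 gives 219 per group for 90% power, and unadjusted power of 24% (33 per arm) to 27% (37 per arm).

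**6. Comparison with 6MWD.** The margin is 0.15 × 467 = 70.05 m. With 33 per arm, SE = 95 × √(2/33) = 23.4 m, and Φ(70.05/23.4 − 1.96) = 85% before any baseline adjustment. The ranking is the reverse of the one stated.

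**7. What passes against 1.51.** The upper CI limit must not exceed 1.51, so the largest observed log ratio that passes is 1.51 − 1.96 × SE. With 33 per arm:

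- Unadjusted: 1.51 − 1.96 × 0.283 = 0.955, a ratio of about 2.6.
- ρ = 0.8: SE = 0.69 × √(2/33) = 0.170, and 1.51 − 0.333 = 1.177, a ratio of about 3.2.

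From a geometric mean of exp(5.04) = 154, these are levels of about 400 and 500.

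**The case against.** The best defence concerns consequences, and several parts of it stand.

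- **The trial size does not depend on this figure.** The 74 comes from 6MWD and the primary calculation (64, or 70 with dropout) uses mPAP. A reader might infer that the trial should have had 808 participants. The documents do not support that: NT-proBNP is a secondary endpoint and its calculation never set the size.
- **The unadjusted figures are the worst case.** SD 1.15 describes spread between patients, and the protocol specifies baseline adjustment. The 25% to 57% range is therefore more relevant than 15%. It is still inadequate, and 85% power with 33 per arm would need a correlation of about 0.95.
- **The margin is not the largest effect that passes.** A reader might infer that a rise in the geometric mean from 154 to 154 × 4.53, about 700, would be called non-inferior. Under the CI rule a true ratio of 4.53 is the null boundary and passes only about 2.5% of the time. The observed ratios that pass are those in step 7. Nor should they be read against the 300 pg/mL in the clinical worsening rule, which is one part of a three-part criterion for individual patients.
- **The test order is not itself an error.** A reader might infer that 6MWD has to come first. The objective-biomarker reason does not depend on the margin, and the protocol accepts that open-label treatment may influence subjective outcomes. Only the power reason fails.
- **The log base is not stated.** Natural logs give a geometric mean of 154 and are the reading kinder to the protocol; base 10 would make 1.51 a 32-fold margin.

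None of this rescues the conversion. The unseen analysis plan does not excuse it either, because the protocol itself states the wrong figure.

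**Conclusion.** The error is confirmed. The log-scale margin is 5.8 times too large (1.51 / 0.262), and the protocol calls a ratio of 4.53 a 30% margin. The 26/29 requirement and the claim of greater power for NT-proBNP are wrong for the chosen margin. At the planned size a true 30% margin gives roughly 15% to 57% power over correlations from 0 to 0.9. These figures assume natural logs, SD 1.15, no true difference and 33 evaluable participants per arm.

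Because 6MWD is formally tested only if NT-proBNP passes, the chance of reaching it can be no higher than the NT-proBNP power, so the 6MWD test would often be blocked. The primary mPAP analysis and the total of 74 are untouched.

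**What to change.** Before any look at outcome data:

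1. State the margin as a geometric-mean ratio of 1.30 (0.262 on the natural-log scale), tested by ANCOVA of log NT-proBNP on log baseline, and name the log base.
2. Delete the 26/29 figure and the sentence claiming greater power than for 6MWD. Give the actual power at the planned size, with the assumed baseline correlation and its source.
3. Re-justify the test order on the biomarker argument alone, acknowledging that a low-power NT-proBNP test would often block 6MWD. Moving 6MWD ahead is one option, not a requirement.
4. If 1.51 is really intended, call it a 4.5-fold margin and justify it clinically.

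The cost is a wording change with no extra participants, plus ethics approval if it counts as a substantial amendment. Timing matters because the trial is open-label, so the change cannot be tied to a later unblinding. The real price is candour: at a 30% margin, 74 participants cannot adequately support a formal NT-proBNP test unless the baseline correlation is very high.

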### Statistical analysis

All analyses will be performed using R (R Foundation for Statistical Computing, Vienna, Austria). Continuous variables will be summarised as mean±SD or median (IQR) as appropriate; categorical variables as counts and percentages. Normality will be assessed using histograms and Q–Q plots. Skewed variables will be log-transformed when necessary.

The null hypothesis is that riociguat discontinuation is inferior to continuation. NI will be concluded if the upper bound of the two-sided 95% CI for the baseline-adjusted between-group difference does not exceed the predefined NI margin. A one-sided significance level of α=0.025 will be used.

A secondary analysis of the primary endpoint (mPAP at 16 weeks) will include an analysis of covariance (ANCOVA), with baseline mPAP as a covariate. Treatment group will be included as the main effect, with riociguat dose and incident/prevalent status included as fixed factors to account for stratification at randomisation. To control the type I error rate, hierarchical testing will be applied. Secondary continuous outcomes will be analysed using ANCOVA or linear regression adjusted for baseline values. Binary outcomes will be analysed using χ^2^ or Fisher’s exact tests. Ordinal outcomes will be analysed using stratified Wilcoxon tests or linear mixed models for repeated measures, as appropriate. All estimates will be reported with two-sided 95% CIs.

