## Methods

### Study design

This is a multicentre, open-label, randomised, controlled NI trial will include 74 CTEPH patients who reached an mPAP <30 mmHg post-BPA, comparing discontinuation versus continuation of riociguat post-BPA. The trial will be conducted at Amsterdam UMC and St. Antonius Hospital, the two Dutch national expert centres for CTEPH. To enhance generalisability, we aim to include additional European centres. Diagnosis of CTEPH, indication for BPA and initiation of riociguat therapy are a part of routine clinical care and fall outside the scope of the trial intervention. The estimated duration of the study is 2.5 years.

Ethical approval was obtained from the Medical Ethics Review Committee Amsterdam UMC (2025.0927) for the trial registered in the Clinical Trials Information System under registration number 2024–5 19 225-38-00.

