### Randomisation and allocation

After confirmation of eligibility and completion of baseline assessments, participants are randomised in a 1:1 ratio to either discontinuation or continuation of riociguat. Randomisation is performed in CastorEDC (Ciwit B.V., Amsterdam, The Netherlands) using block randomisation with variable block sizes. Stratification is applied by riociguat dose at inclusion (daily dose of <6 mg vs ≥6 mg) and time since last BPA, distinguishing incident patients (scheduled for RHC as part of standard clinical follow-up) from prevalent patients (those in long-term follow-up, screened by transthoracic echocardiography (TTE); last RHC performed more than 3 months ago). Due to the nature of the intervention, the trial is conducted as an open-label study. Blinding was considered impractical given the recognisable side effects of riociguat and the objective nature of the majority of primary and key secondary outcomes. However, all physicians performing outcome measurements will be blinded to treatment allocation.

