### Analysis set

The primary analysis will be conducted in the per-protocol population, as an intention-to-treat (ITT) analysis can be considered anticonservative in a NI study testing discontinuation. Participants who restart riociguat due to clinical worsening will be analysed in the continuation group. As a secondary analysis, we will perform an ITT analysis according to randomised allocation, reflecting the clinical discontinuation strategy including re-initiation and testing the safety of the stopping strategy. In addition, two exploratory analyses will be performed: a modified ITT analysis excluding participants who restarted riociguat from the discontinuation group to explore outcomes among patients who tolerate treatment withdrawal without re-initiation, and a subgroup analysis comparing participants who restarted riociguat with the continuation group to assess haemodynamic response following re-initiation. Non-compliant patients who meet protocol violations will be excluded as part of the modified per-protocol (PP) analysis. Missing data will not be imputed. However, participants who withdraw before the week 8 clinical worsening assessment because of clinical deterioration, or for whom the reason for withdrawal is unknown, will be conservatively classified as having experienced clinical worsening.

To account for potential loss of participants from the primary per-protocol analysis due to clinical worsening, predefined scenarios were incorporated into the statistical analysis planning. Based on power simulations, the study is expected to retain approximately 80% power if up to 35% of participants are lost from the intervention group. To mitigate the risk of insufficient power, the randomisation ratio will be reassessed after inclusion of 50% of the planned sample size. If ≥30% or ≥40% of participants in the discontinuation group have restarted riociguat at that point, the randomisation ratio will be adaptively adjusted from 1:1 to 2:1 or 3:1, respectively, in favour of the discontinuation group. If ≥50% of participants in the discontinuation group experience clinical worsening, the study will be terminated for safety reasons, as such a rate is considered clinically unacceptable.

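### If the allocation ratio changes midway, no described analysis has a term for allocation stage or centre, so a period difference left after baseline adjustment would enter the treatment effect

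*Protocol article*

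**What the plan says.** Under Randomisation and allocation, "Stratification is applied by riociguat dose at inclusion" (below 6 mg a day v 6 mg or more) and by incident or prevalent status. Centre is not a stratum.

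Under Statistical analysis, non-inferiority is judged on a baseline-adjusted difference whose other terms are not listed. A secondary ANCOVA for mPAP has baseline mPAP and treatment, "with riociguat dose and incident/prevalent status included as fixed factors to account for stratification at randomisation". The secondary continuous outcomes, which include NT-proBNP and 6MWD, are adjusted for their baseline values. Neither centre nor allocation stage is named for any of these.

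Two other sections make this matter. Study design names two Dutch centres and adds: "To enhance generalisability, we aim to include additional European centres". Analysis set calls for a review at half of the planned inclusion, at which "the randomisation ratio will be adaptively adjusted from 1:1 to 2:1 or 3:1" if at least 30% or 40% of the discontinuation group have restarted riociguat. That section also places participants who restart for clinical worsening in the continuation group for the primary per-protocol analysis, and makes intention-to-treat secondary.

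**The concern.** Once the ratio changes, the chance of being allocated to discontinuation depends on when a participant was enrolled. Randomisation still makes the arms comparable within each stage, but not after the two stages are pooled. Later participants are then over-represented in the discontinuation arm by design. If they differ from earlier ones in 16-week mPAP, NT-proBNP or 6MWD after baseline adjustment, part of that difference is read as a treatment effect. New centres, altered case mix or drift in practice could each produce such a difference.

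The bias can go either way. One direction costs power. The other makes stopping riociguat look safer than it is, which is the more serious error in a non-inferiority trial of withdrawal.

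**Working it through.** **Inputs from the article.** Total 74, review at 37, ratio 1:1 and then 2:1 or 3:1, triggers 30% and 40% restarts, "assuming a one-sided α of 0.025, power of 90%, SD of 4.9 mmHg and an NI margin of 4 mmHg".

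**The plan's own figure.** n per group = (1.960 + 1.282)² × 2 × 4.9² / 4² = 31.5, so 32 per group and 64 in all. This agrees with the article: "64 participants (32 per group) are required". The total of 74 comes from 6MWD.

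**Assumption.** The article gives no earlier-to-later difference. I take a residual difference of 2 mmHg in mPAP after baseline adjustment, with a range of 1 to 3.

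**Step 1: randomised arms (intention-to-treat).** The first 37 split 18.5 and 18.5.
- 2:1: the next 37 split 24.67 and 12.33. Later share: 24.67/43.17 = 57.1% v 12.33/30.83 = 40.0%. Gap 0.171.
- 3:1: the next 37 split 27.75 and 9.25. Later share: 27.75/46.25 = 60.0% v 9.25/27.75 = 33.3%. Gap 0.267.

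**Step 2: primary per-protocol set.** Restarters move to continuation. I apply the trigger rate in both stages and ignore other exclusions.
- 2:1, 30% restart: discontinuation keeps 12.95 earlier and 17.27 later (57.1% later). Continuation becomes 18.5 + 5.55 = 24.05 earlier and 12.33 + 7.40 = 19.73 later (45.1% later). Gap 0.121.
- 3:1, 40% restart: discontinuation keeps 11.10 and 16.65 (60.0% later). Continuation becomes 18.5 + 7.40 = 25.90 and 9.25 + 11.10 = 20.35 (44.0% later). Gap 0.160.

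**Step 3: bias and error rate.** Bias = gap × residual difference. SE = 4.9 × √(1/n₁ + 1/n₂) for all 74. If the bias favours discontinuation, one-sided type I error = Φ(−1.96 + bias/SE), against the planned level: "A one-sided significance level of α=0.025 will be used".

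| Set and ratio | SE (mmHg) | Bias at 1 / 2 / 3 mmHg | Type I error at 1 / 2 / 3 mmHg |
|---|---|---|---|
| Intention-to-treat, 2:1 | 1.155 | 0.17 / 0.34 / 0.51 | 0.035 / 0.048 / 0.065 |
| Intention-to-treat, 3:1 | 1.177 | 0.27 / 0.53 / 0.80 | 0.042 / 0.066 / 0.100 |
| Per-protocol, 2:1 | 1.159 | 0.12 / 0.24 / 0.36 | 0.032 / 0.040 / 0.050 |
| Per-protocol, 3:1 | 1.177 | 0.16 / 0.32 / 0.48 | 0.034 / 0.046 / 0.060 |

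In the other direction, power = Φ((4 − bias)/SE − 1.96). At 2 mmHg, intention-to-treat power falls from 93% to 89% (2:1) or from 92% to 84% (3:1). If the difference comes only from new centres and they supply half of the later participants, the bias halves.

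**Step 4: a stable centre offset.** The Non-inferiority margin section gives a baseline SD of 3.43, a change SD of 3.8 and a correlation of −0.08. The slope of follow-up on baseline is therefore 1 − 0.08 × 3.8/3.43 = 0.91. An offset of 2 mmHg present at both visits leaves 2 × 0.0886 = 0.18 mmHg. Times the gaps, that is 0.03 (2:1) or 0.05 mmHg (3:1) in intention-to-treat, and 0.02 or 0.03 mmHg per protocol.

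**Step 5: ratio stays 1:1.** There is no systematic gap. With two equal centres, the 95% range of chance imbalance in centre share is 1.96 × √(0.25 × 4/74) = ±0.23, or ±0.46 mmHg for a residual centre difference of 2 mmHg. Adjusting for centre would cut the SD from 4.9 to √(4.9² − 2²/4) = 4.80 and the size before dropout from 64 to 62. At 1 mmHg it stays at 64.

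**The case against.** The strongest reply has four parts.

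- **The covariate lists are not closed.** The model with listed factors is a secondary analysis, and full model terms are often left to the analysis plan. This is fair as to wording. Still, the article sets out both the adaptation and the factors that account for the randomisation, and the second does not reflect the first.
- **Baseline adjustment already deals with centre.** The three non-inferiority outcomes are measured at baseline and again at 16 weeks. For a stable offset this stands, as step 4 shows. It does not cover a difference in 16-week change between earlier and later participants.
- **Counting restarters as continuing narrows the gap in the primary analysis.** This stands and is carried through in step 2. The wider gap applies to intention-to-treat.
- **Several conditions must coincide.** Restarts must reach 30%, and the later participants must differ after adjustment. For the centre route, new centres must also join, mainly in the second half; they are only an aim, with no number or timing given. This stands. The bias is a possibility, not a forecast.

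A reader might also infer that centre should have been a stratification factor. The article does not support that: two binary factors already give four strata, three centre levels would give twelve, and 74/12 is about six participants per stratum. Nor does it support reading ordinary differences between centres in measurement as a threat of 2 mmHg or so. Local measurement is itself only inferred, because no central reading is described.

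**Conclusion.** The concern holds as a conditional gap: the plan prespecifies a ratio change and describes no analysis that accounts for it. If the change happens, a residual period or centre-mix difference of 1 to 3 mmHg would move the mPAP comparison by 0.12 to 0.48 mmHg per protocol and 0.17 to 0.80 mmHg in intention-to-treat. That is small beside the 4 mmHg margin but not beside a standard error of about 1.16 to 1.18 mmHg. At 2 mmHg the one-sided error would be about 0.040 to 0.046 per protocol and 0.048 to 0.066 in intention-to-treat.

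These figures rest on the assumed residual difference, equal restart rates in both stages at the trigger values, SD 4.9, a normal approximation and no dropout. It would go too far to say that the trial as planned is biased: with 1:1 throughout, leaving out centre costs only balance and a little precision.

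**What to change.** State before the half-way review that, if the ratio is changed, allocation stage (before or after the change) is a fixed factor in the mPAP, NT-proBNP and 6MWD models, in both the per-protocol and intention-to-treat analyses. Include centre in the same models as a fixed factor, with one level for each Dutch centre and all later centres pooled.

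The cost is one to three degrees of freedom from about 66 evaluable participants (74 less 10%) and a few lines of text. No extra participants and no change to stratification are needed. Prespecifying the terms now avoids their looking post hoc.

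### The models stated for the NT-proBNP and 6MWD non-inferiority tests name only the baseline value, while the mPAP ANCOVA also carries the two stratification factors; available precision may be forgone

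*Protocol article*

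**What the plan says.** All references are to the Protocol article.

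- **Randomisation and allocation:** "Stratification is applied by riociguat dose at inclusion (daily dose of <6 mg vs ≥6 mg) and time since last BPA", the latter split into incident and prevalent patients. Blocks are of variable size and "participants are randomised in a 1:1 ratio to either discontinuation or continuation of riociguat".
- **Statistical analysis, mPAP:** the ANCOVA, described as a secondary analysis of the primary endpoint, has baseline mPAP as covariate, "with riociguat dose and incident/prevalent status included as fixed factors to account for stratification at randomisation".
- **Statistical analysis, other continuous outcomes:** "Secondary continuous outcomes will be analysed using ANCOVA or linear regression adjusted for baseline values". No stratification factor is named.
- **Statistical analysis, decision rule:** "NI will be concluded if the upper bound of the two-sided 95% CI for the baseline-adjusted between-group difference does not exceed the predefined NI margin". The rule mentions baseline adjustment and nothing else. "A one-sided significance level of α=0.025 will be used".
- **Objectives and endpoints, Table 1:** the first two secondary endpoints in the hierarchy are "NT-proBNP (assessed for non-inferiority) 6MWD (assessed for non-inferiority").
- **Sample size calculation:** "For 6MWD, a NI margin of 15% was used". With a mean of 467 m and an SD of 95 m, this gives 33 per group at 85% power and sets the total of 74.

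**The concern.** One paragraph states two models for continuous outcomes. The first includes the stratification factors and gives the reason, which is that randomisation used them. The second leaves them out without comment, although that reason applies equally to it. Ordinal outcomes may also be given a stratified test, so the secondary continuous outcomes are the exception.

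Stratified allocation balances the arms on the two factors. If a factor predicts the outcome, that balance removes its contribution from the sampling error of the treatment difference. A model without the factor leaves the same contribution in the residual variance. The reported standard error then exceeds the true one, the confidence interval is wider than it need be, and the one-sided test runs below 2.5%. In a non-inferiority trial the interval is the decision, so unneeded width costs power. 6MWD is where it could show: it has the lowest planned power of the three sized endpoints and it fixes the trial size.

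**Working it through.** **Inputs from the Sample size calculation section.** 6MWD: SD 95 m, margin 0.15 × 467 = 70.05 m, 33 per group, one-sided alpha 0.025. NT-proBNP: log-scale SD 1.15, margin 1.51.

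**Assumptions (not in the documents).** R² is the share of the outcome variance left after baseline that the strata explain. ρ is the correlation of baseline with 16-week 6MWD. There are four equally likely strata, with blocks of 2 or 4.

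**1. Reproduce the plan's figure.** n = 2 × 95² × (1.960 + 1.036)² / 70.05² = 33.03 per group, against 33 stated. Power at 33 per group: 70.05 / (95 × √(2/33)) − 1.960 = 2.995 − 1.960 = 1.035, which gives 85.0%. Dropout: 66 / 0.9 = 73.3, so 74. The plan's figure is reproduced. It uses the full SD, with no reduction for baseline or strata.

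**2. Possible gain in precision.** Adding the strata multiplies the interval half-width by √(1 − R²): 1.00 at R² = 0, 0.975 at 0.05, 0.949 at 0.10 and 0.894 at 0.20.

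**3. Compare the two models under stratified allocation.** 6MWD was simulated with 66 patients and 6,000 runs per setting. Each pair of results is baseline only, then baseline plus strata.

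| ρ | R² | Half-width (m) | Power (%) | One-sided type I error (%) |
|---|---|---|---|---|
| 0 | 0 | 46.9, 47.0 | 83.2, 82.9 | 2.6, 2.5 |
| 0 | 0.05 | 46.9, 45.8 | 83.2, 84.1 | 2.3, 2.7 |
| 0 | 0.10 | 46.9, 44.6 | 83.9, 86.5 | 2.0, 2.6 |
| 0 | 0.20 | 47.0, 42.0 | 85.4, 90.2 | 1.4, 2.5 |
| 0.5 | 0 | 40.6, 40.7 | 92.4, 92.4 | 2.4, 2.4 |
| 0.5 | 0.10 | 40.7, 38.6 | 93.0, 94.5 | 1.8, 2.4 |
| 0.5 | 0.20 | 40.8, 36.4 | 94.0, 96.3 | 1.4, 2.3 |

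The Monte Carlo standard error of a type I entry is √(0.025 × 0.975 / 6,000) = 0.2 points. The power of 83% in the first row, against 85% in step 1, reflects the t distribution and the estimated variance. It appears in both models and is not caused by omitting the strata.

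The mechanism shows at ρ = 0, R² = 0.20. The baseline-only model reports a standard error of about 47.04 / 1.998 = 23.5 m, while the estimate's actual standard deviation over the runs is 21.3 m.

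**4. Let baseline carry the stratum effect.** Above, the strata act independently of baseline. If instead the strata shift 6MWD equally at baseline and at 16 weeks, power is 94.3% against 94.4% (R² 0.10) and 96.2% against 96.5% (R² 0.20) at a within-stratum correlation of 0.5. At 0.7 it is 99.1% against 99.0%, and 99.6% against 99.5%. The loss is then about half a point at most.

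**5. NT-proBNP.** At the stated margin and 33 per group, without strata: 1.51 / (1.15 × √(2/33)) − 1.960 = 5.33 − 1.96 = 3.37, so power is above 99.9%. There is practically nothing to gain.

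**The case against.** The strongest reply has four parts.

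**The wording is condensed.** The sentence does not say baseline values alone, and a full covariate list is commonly left to the SAP. This limits the point but does not remove it. The article does state a model here, and the preceding sentences name the strata and the reason for them, so omission is the natural reading. A SAP that followed the sentence would inherit the difference.

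**The size depends on unknowns.** Nothing in the article says that dose stratum or incident/prevalent status predicts 6MWD or NT-proBNP. Baseline 6MWD is measured and in the model, and may carry most of any stable stratum effect. This stands. It is why the loss has to be given as a range that starts at zero.

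**Stronger readings fail.** A reader might infer that the trial misses its planned power. It does not on this account: the 85% assumes no covariate gain, so what is forgone is a bonus. A reader might infer a raised risk of falsely declaring non-inferiority. Under the stratified allocation the error goes the other way. A reader might infer that both named tests lose power. For NT-proBNP that is not so at the stated margin of 1.51. A much smaller log margin would make its precision matter more, but that is a separate question about the margin.

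**The balance may not survive intact.** The Analysis set section moves restarters into the continuation group for the per-protocol analysis and allows a change to 2:1 or 3:1 allocation. Both can weaken the within-stratum balance on which the overstated standard error depends, and the simulation does not model them. This stands as a limit on the figures. It is no argument for leaving the strata out, because adjustment also protects against any imbalance in stratum mix that results.

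**Conclusion.** The point holds as a minor one. The article adjusts the mPAP ANCOVA for the randomisation strata and states baseline-adjusted models without them for the secondary continuous outcomes, including two formal non-inferiority tests. The possible loss of 6MWD power, for an assumed strata R² up to 0.20, is:

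- none if the strata explain nothing;
- about 2 to 5 points at R² 0.10 to 0.20 if baseline is uninformative;
- about 1.5 to 2.3 points over the same range if baseline correlates 0.5 with the outcome and the strata act independently of it;
- about half a point or less if baseline carries the stratum effect.

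The figures rest on assumed values of R², ρ, stratum sizes and block sizes, and on analysis by randomised allocation.

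**What to change.** Replace the sentence on secondary continuous outcomes with wording such as: *NT-proBNP (log scale), 6MWD and the other secondary continuous outcomes will be analysed by ANCOVA with treatment group, the baseline value of the outcome, riociguat dose stratum (below 6 mg, or 6 mg and above, daily) and incident/prevalent status, as in the mPAP ANCOVA.* In the decision rule, state that the adjusted difference compared with each non-inferiority margin comes from a model with these same covariates, so that the mPAP test is covered too.

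The cost is one or two sentences and two degrees of freedom per model. No new data are needed, since both factors are recorded at randomisation. If the strata explain nothing, the price is about 0.3 points of 6MWD power or less (83.2% against 82.9% at ρ = 0, no difference at ρ = 0.5). The change should be made before outcome data are seen.
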